### Participants and recruitment

Participants are recruited from psychiatric healthcare settings at participating centres, including inpatient psychiatric wards, outpatient psychiatric services, emergency care, and medical wards via consultation liaison services. Patients (65+) who have been hospitalised (minimum 1 night) in connection with a suicide attempt during the last 3 months or an episode of serious suicidal planning during the last month at any of the participating clinics are eligible for participation in the study. Unit managers, doctors and medical staff working in the inpatient wards, outpatient clinics and consultation psychiatric services will be informed about the study and asked to identify potential participants and provide interested patients with oral and written information about the trial.

Individuals who meet the eligibility criteria (see below) are invited to a brief screening to confirm their suitability for the study. If they remain eligible and wish to receive more information, the staff will provide detailed study information, which participants can review at their own pace. They will also have the opportunity to ask questions, which can be addressed by the study researcher as needed. The study researcher will then contact the patient to discuss the research details and answer any remaining questions. If the patient chooses to enrol, they will sign the consent form, and baseline measurements will begin. After the baseline assessment, the participant is randomised to either the intervention group (ASSIP OA + TAU) or the control group (TAU). Participants receive information about allocation in connection with the baseline visit, along with information about their scheduled appointment with an ASSIP-OA therapist or their next scheduled research assessment.

All quantitative data will be securely stored in REDCap and presented at the group level to ensure anonymity.

### Eligibility criteria

#### Inclusion criteria

Age 65 and above at time of index suicide attempt or hospitalisation for serious suicidal plans.A mental health care contact during the active treatment period.Capable of understanding study procedures and providing informed consent.

#### Exclusion criteria

Clinical diagnosis of dementia or Montreal Cognitive Assessment (MoCa) score less than − 2 standard deviations from the normative score for education and age [31]. Ongoing delirium, or any other condition impeding the comprehension of the study’s procedures and implications that hinder the provision of informed consent.Severe ongoing psychosis, severe ongoing substance use disorder, emotionally instable personality syndrome and any other condition that would require longer specialized treatment to reduce future suicidal behaviour (e.g. DBT).Terminal illness.Insufficient knowledge of the Swedish language (requires interpreter).Aphasia or other severe communication issue or severe hearing and/or severe visual impairment despite corrective aids that render the intervention unfeasible.

In connection with post-treatment data collection, a purposive sample of approximately 15 participants who took part in ASSIP-OA sessions will be asked to participate in an interview to generate a deeper picture of participants’ experiences of ASSIP-OA. In addition, we will use focus group interviews to examine ASSIP-OA therapists’ experiences of the training and application of ASSIP-OA in their clinical settings, including their experiences of obstacles and opportunities in connection with the delivery of ASSIP-OA. We anticipate that all the ASSIP-OA therapists (n = approx. 14) will be interested in taking part in two sets of focus groups, but participation is voluntary.

### Sample size

A total of 132 participants will be included in the trial. The power calculation, i.e., the number of participants needed in each intervention group, is based on the previous ASSIP study of [name] and colleagues [17]. In that study, 26.7% of the participants in the control group, usual treatment, and 8.3% in their intervention group, ASSIP, reattempted suicide during follow-up. Based on clinical experience as well as prospective data from our previous multicentre study [12] for persons 65 + receiving usual treatment, we choose to calculate power based on an expected repetition risk of 30% in our control group (usual treatment), and 10% in our intervention group receiving ASSIP-OA plus TAU. Furthermore, given a desired power of 0.80 (a 4/5 chance of discovering an effect if it exists, regarded as adequate in this context) and a risk level of 5%, 60 participants in each condition is needed. We further expect a dropout rate of 10%, thus each group will therefore comprise 66 participants.

### Therapists

The therapists (psychiatrists, psychologists, nurses in psychiatric care, or social workers) all work as mental health professionals at the participating clinics, and all have clinical experience with suicidal patients. Presumptive ASSIP-OA therapists are required to have basic education in psychotherapy. The training to become a certified ASSIP therapist includes two days of theoretical lectures and skills training followed by supervision for approximately one year (5 patients under supervision, supervision on every session). The ASSIP-OA therapist training also includes theoretical lectures about suicidal behaviour in older adults as well as information about how the intervention has been modified to apply to older participants. The ASSIP-OA therapists are trained by a certified ASSIP supervisor ([name]), as well as clinical gerontologists experienced in geriatric psychiatry. Only fully trained and certified ASSIP therapists or therapists in training with supervision after each session will conduct ASSIP-OA sessions with participants in this study. During the course of the project, the ASSIP-OA therapists have group meetings and continued regular supervision in groups or individually even after certification.

### Interventions

#### Treatment group

The treatment group will receive TAU with the addition of a modified versionof ASSIP. The full treatment protocol for ASSIP-OA is described in Table 1. The novelty of this program for older adults and the main modifications include:

Flexibility in treatment delivery, such as offering home visits, breaks and shorter/longer sessions as needed.Optional additional session together with one or two close relatives or other support person(s), chosen by the participant.Optional additional session to further train safety strategies (may be needed more frequently for participants with MCI or other disabilities).Homework, letters, and case conceptualization adapted linguistically and content-wise to the target group.ASSIP-OA also includes participants with a suicidal crisis (e.g. suicide plans/thoughts requiring hospital care).

Clinical psychologists and a psychiatrist, experienced in geriatric psychiatry in Sweden, have drawn on insights from the geriatric psychiatry clinic in Bern (personal communication, [name], 2025) to tailor the treatment protocol to the Swedish context. [name] stresses that it is not the specific components of ASSIP that require change, but rather that there should be a greater focus on the patient’s individual needs of support in areas such as loneliness, chronic pain, physical limitations and in some cases milder cognitive impairment. [name] highlights the need for a higher degree of flexibility when delivering ASSIP to older adults, especially for the “older older”. Providing home visits is one way to improve adherence [32]. Older adults may require extra support in communicating their needs. As most suicidal older adults are dealing with chronic medical conditions and have regular appointments with primary care, it is important to share the case conceptualisation with the patient’s GP and other relevant care providers, once permission is given by the patient. Moving to long term care was a particularly vulnerable time for older adults at the Bern clinic, an observation we have also made in our own Swedish research [33]. In such cases, ASSIP could better fit the older person’s needs by including a session with a nurse or other staff member at the care facility, chosen by the older adult, after the tree core sessions to support the translation of ASSIP warning signs and coping strategies into everyday life. Another reflection from the Bern clinical experience was that, while the video playback was not an issue for most older participants, some older men found it problematic to watch. This could be ameliorated by the therapist taking a more supportive role than they might have done with a younger patient. A more active role by the therapist may also be appropriate for older adults experiencing cognitive impairment. Enhancing problem-solving abilities is a key component of treatment protocols for individuals with suicidal tendencies and executive dysfunction [34].

**Table 1 Tab1:** Treatment protocol for the attempted suicide short intervention program for older adults (ASSIP-OA)

Session no	Session Components and Modifications
1	**Narrative interview.** Narrative interview focusing on the background of the suicidal crisis. At the end of session 1 the patient receives a psychoeducational text to read and comment on as homework. The homework has been modified by psychologists ([name], [name] and [name]) with experience in geriatric psychiatry together with a certified ASSIP instructor and supervisor ([name]). In addition, an older adult (80+) with lived experience of attempted suicide has contributed to the revision of the homework.
2	**Video playback.** Starts with collaborative with the patient’s comments in the homework text. The patient and therapist then watch the video recording from session 1 together, periodically pausing the video to comment and add information.
3	**Collaborative case conceptualisation.** Compilation of a written case conceptualisation of the individual’s vulnerability, triggering events, and suicidal process that preceded the suicidal crisis. Long-term therapy goals, warnings signs, and safety strategies revealed and developed (during video-playback) by the patient and the therapist collaboratively are revised and compiled into a list on an easily accessible card, including phone numbers to easy access relevant care services, helplines, and people whom the patient chooses and trusts. A copy of the case conceptualization, including safety measures, and long-term goals is sent to the patient’s physician as well as to other relevant care providers. The ASSIP-OA intervention may end here, or further sessions may be relevant as described below.
4 (optional)	**Rehearsal session.** This session, which is optional also in the original ASSIP program, may be particularly relevant for older adults with mild cognitive impairment or other functional limitations who may require an extra session to further train safety strategies.
5 (optional)	**Session including support person.** This session (a modification not included in the original ASSIP) invites one or two close relatives or other support person(s), chosen by the participant. The patient shares his/her formulation of preventive measures, and a dialog follows, with a focus on how safety measures learned in ASSIP-OA can be translated into everyday life.
Letters	**Letters.** After completion the last ASSIP-OA session, therapists will send semi-standardised letters every third month during the first year and biannually during the second year. The purpose of these letters is to provide hope and psychological support, as well as providing participants with a gentle reminder to make use of their personalised coping strategies. The patient is encouraged to contact their ASSIP-OA therapist, either to update them on their well-being or if they experience a new suicidal crisis. In the latter case, the participant’s physician is informed, and the ASSIP-OA therapist can offer a booster session for additional support facilitating access to the healthcare system as needed, with a renewed conceptualisation and updated formulation on safety measures. The session can be provided in hospital as needed. A copy of the updated materials is sent to the participant’s physician.
Non session specific modifications in ASSIP-OA	A higher flexibility when delivering ASSIP-OA, providing the opportunity for home delivered session if needed. Depending on physical and cognitive functioning, flexibility in session length and breaks is advisable. A more active role on the part of the therapist could also be relevant for older adults who suffer from mild cognitive impairment. Linguistically and content-wise modifications to suite the target group, adjusted homework, letters, and case conceptualisation.

#### Control group

Participants randomised to the control group will receive TAU in line with the regional and national guidelines. Treatment as usual (TAU) was selected as the comparator to reflect the standard care typically provided to suicidal older adults in real-world clinical settings. TAU may vary between the participating hospitals. The cornerstone of treatment as usual for suicidal older adults consists of antidepressant medication, alone or in combination with other types of psychoactive drugs (sedatives/antipsychotics/hypnotics/mood stabilisers). Persons with serious or treatment-resistant depression may be offered electroconvulsive therapy (ECT). Some persons may receive supportive/therapeutic contacts with mental health professionals (nurses/social workers/psychologists) but no psychosocial interventions designed specifically for suicidal older adults are offered as part of ordinary treatment at the participating clinics.

### Screening

Potential participants receive written information about the research project prior to screening. The screening begins with information about what it means to be part of the study. In order to determine eligibility, the short form of the Columbia Suicide Severity Rating Scale (C-SSRS) [35] is employed to investigate suicidal planning and behaviour. The Montreal Cognitive Assessment (MoCA) [36] is applied for cognitive screening. Severe ongoing psychosis, severe ongoing substance use disorder and emotionally instable personality syndrome are screened through the patients’ medical record. The screening procedure takes place at the patient’s ward/outpatient clinic.

### Sociodemographic and clinical characteristics

To characterise participants, data on demographic variables including age, sex (woman, man, non-binary or other), marital status, ethnicity, education level, and occupation prior to retirement will be gathered after study inclusion.

The Trail Making Test (TMT part A and B) [37] will be employed to assess executive function. The full (original) version of the Columbia-Suicide-Severity-Rating Scale (C-SSRS) [35] will be administered by the interviewer for history of suicidal episodes and to provide information for a global clinical risk assessment (the short form of the C-SSRS has been administered at the screening, see Fig. 1). For actual suicide attempts, suicidal intent is measured with Beck’s Suicide Intent Scale (SIS) [38]. Overall health burden will be rated with the Cumulative Illness Rating Scale for Geriatrics (CIRS-G) [39]. Alcohol use will be self-reported at this time with the Alcohol Use Disorders Identification Test (AUDIT) [40], and persons who acknowledge drug use will complete the Drug Use Disorders Identification Test (DUDIT) [41].

### Outcome measures

#### Primary outcome

The primary outcome variable at 6-, 12- and 24-month follow-up is any “new suicidal episode,” a composite rating that is coded “yes” in the event of (a) a new suicide attempt as registered in the participant’s medical record or the national hospital register or (b) suicide death as registered in the national cause of death register.

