## Objectives and hypothesis

This paper outlines the study protocol for our upcoming study, which aims to evaluate a modified version of the Attempted Suicide Short Intervention Program (ASSIP), specifically for older adults (65+), the ASSIP for older adults (ASSIP-OA), as an add-on to usual treatment. The efficacy of the ASSIP-OA intervention will be evaluated by comparing it to a control group receiving only treatment as usual (TAU).

The main hypothesis is that participants randomised to the add-on treatment condition - the ASSIP-OA intervention - will experience a preventive effect on suicide and suicide attempts within 6, 12, and 24 months following the index episode. Also, we anticipate participants in the experimental condition to show better improvement in psychiatric symptoms/severity of suicidal ideation/coping skills/quality of life (secondary outcomes). Additionally, we aim to investigate if the brief preventive intervention (ASSIP-OA) is feasible, based on its acceptability, appropriateness, deliverability and fidelity, and whether participants have fewer days of inpatient care or experience any negative side effects. Further, the study also includes a qualitative approach to explore what kind of challenges and opportunities (a) older adults and (b) ASSIP-OA therapists experience in relation to implementing the brief preventive intervention, and if the modifications that we made in ASSIP-OA are relevant for older adults.

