### Data analysis

We will use an intention-to-treat analysis. The primary outcome will be analysed using chi-square analyses. The secondary outcomes will be analysed using a so-called “mixed effect model approach” with the aim of examining changes before and after treatment as well as during the follow-ups. This approach can take into account data clustering and covariates as well as possible dropouts.

We will examine effects both between and within groups, to be able to determine if the preventive intervention ASSIP-OA in addition to TAU has a better effect than the control group, treatment as usual (TAU), after the intervention (between-group effect). Further, we want to find out whether ASSIP-OA and the control group have improved over time (within-group effect) and, if the ASSIP-OA has any effect, whether such effect is “driven” by the ASSIP-OA (interaction effect). The statistical approach is based on regression analyses. Contrary to more traditional variable-oriented analyses for repeated measurements, it has the benefit of taking into consideration the fact that data are not independent at repeated measurements over time and provides better handling of missing data by incorporating all available information. This method is now regarded as preferable to using more traditional methods for missing data in clinical studies.

For qualitative data collected through individual and focus group interviews, transcribed interviews will be analysed, and themes and subthemes will be identified and categorised following Braun and Clarke’s thematic analysis [51].

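### The primary outcome is set at 6, 12 and 24 months with no deciding time point, so the stated 5% error and 0.80 power hold together only if one of the three is named

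*Protocol article*

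**What the plan says.** All of this is in the protocol article.

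- **Primary outcome:** "The primary outcome variable at 6-, 12- and 24-month follow-up is any" new suicidal episode, a yes/no composite of a recorded suicide attempt or a suicide death. No month is ranked above another.
- **Objectives and hypothesis:** the main hypothesis is a preventive effect on "suicide and suicide attempts within 6, 12, and 24 months following the index episode", again unranked.
- **Data analysis:** "The primary outcome will be analysed using chi-square analyses". The mixed model described there is for the secondary outcomes only.
- **Sample size:** the trial is sized on an "expected repetition risk of 30% in our control group (usual treatment), and 10% in our intervention group receiving ASSIP-OA plus TAU", "given a desired power of 0.80" and "a risk level of 5%, 60 participants in each condition is needed". The source trial's rates are given as the share who "reattempted suicide during follow-up", with no month. Then: "We further expect a dropout rate of 10%, thus each group will therefore comprise 66 participants".

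**The concern.** The sample-size section budgets for one test of one pair of risks. The outcome and hypothesis sections offer three occasions for that test. A chi-square test handles one two-by-two table at a time, so the analysis does not merge the three occasions into a single result.

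Without a deciding month, the reader cannot tell what a positive trial is. Suppose the trial is significant at 6 months and not at 24, or the reverse. The article does not say whether the main hypothesis is then supported, and the choice could be made after the results are known. Which time point decides the trial is part of the definition of the primary outcome, and here that definition states three.

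**Working it through.** **1. Reproduce the stated sample size.** Inputs from the Sample size section: risks 0.30 and 0.10, error 5%, power 0.80. Sidedness is not stated; two-sided is used, with z = 1.960 and 0.842.

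- Unpooled: n = (1.960 + 0.842)² × (0.30×0.70 + 0.10×0.90) / 0.20² = 58.9, so 59 per arm.
- Arcsine: h = 2(arcsin√0.30 − arcsin√0.10); n = 2(2.802/h)² = 59.01, so 60 per arm.
- Pooled: n = (1.960√(2×0.20×0.80) + 0.842√0.30)² / 0.20² = 61.6, so 62 per arm.
- One-sided 5%, pooled: 49 per arm.

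The stated 60 is therefore a two-sided 5% calculation for **one** comparison. Power at 60 per arm is 79% by the pooled normal formula and 80.2% by exact calculation. The allowance for dropout is 60 × 1.10 = 66 per arm, 132 in total.

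**2. Assumptions for three looks.** The article does not say how events spread over the 24 months, so the timing is assumed. The share of 24-month events that have occurred by 6 and 12 months is set at 25/50%, 40/65%, 50/75% or 60/80%. The outcome is cumulative, so the tests are correlated. For risks p(s) < p(t) at two months, the correlation is √[p(s)(1 − p(t)) / (p(t)(1 − p(s)))]. For example, with 7.5% at 6 months and 30% at 24 months it is √(0.0525/0.2775) = 0.43. Across the scenarios it runs from 0.43 to 0.88. Three independent tests would give an upper reference of 1 − 0.95³ = 14.3%.

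**3. If any one of three may count.** These are simulations under no effect, with a 24-month risk of 30% in both arms, 300,000 trials per scenario, and chi-square at two-sided 5% at each month. The entries are the chance of at least one p < 0.05.

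| Events by 6/12 months (assumed) | Uncorrected, 60 per arm | Uncorrected, 66 per arm | Continuity-corrected, 60 / 66 per arm |
|---|---|---|---|
| 25/50% | 11.8% | 11.8% | 6.2% / 6.6% |
| 40/65% | 11.0% | 10.7% | 6.3% / 6.7% |
| 50/75% | 10.4% | 10.2% | 6.2% / 6.6% |
| 60/80% | 9.8% | 9.6% | 5.9% / 6.2% |

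At 24-month risks of 10% or 20% the uncorrected rate is 9.2-11.6%, and the corrected rate about 3-6%. Counting only false claims of benefit, the uncorrected rate is 4.6-6.0% over all scenarios, against a nominal 2.5%.

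**4. If all three must be significant.** The false-positive rate cannot exceed 5%. For power, assume 30% against 10% at 24 months and the same proportional effect at each month, so that the 25/50% scenario has 7.5% against 2.5% at 6 months. Simulated power to succeed at all three is 18-49% at 60 per arm and 21-54% at 66. The 6-month comparison, with few events, is the bottleneck.

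**5. If one month decides.** The error rate is the nominal 5%, and step 1 stands unchanged provided the 30% and 10% belong to that month.

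**6. If the error is split over three routes.** Bonferroni (0.05/3 = 0.0167) lowers power at 60 per arm from 79% to 64% by the pooled formula, or from 80.2% to 65.7% by exact calculation. Restoring 80% would need about 83 per arm, or 92-93 with 10% dropout.

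**The case against.** A reader might infer that the plan lets a significant result at any of the three months count, and hence that the trial's false-positive rate simply is 10-12%. The documents do not support that. No section states such a rule, and the hypothesis joins the three months with *and*, which can be read as requiring an effect at each. The plural in the analysis section is weak evidence either way. The figure also depends on assumed event timing and on uncorrected tests, and the article does not say whether a continuity correction is used. It counts false findings of harm as well, which could not support a hypothesis of prevention. These points stand, and they are why the size is given here only with its conditions. They do not remove the defect, because the conjunctive reading gives up the stated power.

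It can also be said that the powered month is inferable. The Background reports the source trial's reduction in attempts over 24 months, so 30% and 10% are most naturally 24-month risks. That is fair. It supports 24 months as the choice, but the outcome and hypothesis sections still give the other two months equal standing.

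Testing order and the sharing of the error rate are commonly left to an analysis plan, which is not shown, and their absence is not held against the article. The primary time point is different: it belongs to the outcome definition, which the article does give. Lastly, all three months are declared in advance, which limits undisclosed selection. It does not settle which of the three decides.

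**Conclusion.** The concern holds in this form: three primary time points, no deciding one, and a sample size for a single comparison whose month is not stated. The article's 5% and 0.80 are both true only if one time point decides.

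The size depends on the rule eventually adopted. Under any-one-of-three with uncorrected two-sided tests, and with no multiplicity control set elsewhere, the false-positive rate is roughly 9-12%. With a continuity correction it is about 6-7% at a 30% risk and lower at smaller risks. Under all-three there is no inflation, but power is about 18-54%. Both ranges rest on assumed event timing, and the power range also on a constant proportional effect.

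**What to change.** - In the Primary outcome section and the main hypothesis, name the 24-month comparison as the single primary test, at two-sided 5%.
- In the Sample size section, state that 30% and 10% are 24-month risks. This agrees with the 24-month result cited in the Background.
- In the Data analysis section, make 6 and 12 months secondary, either descriptive or tested in a fixed order only after 24 months succeeds.
- Make the same change in the trial registration, by the modification route described under Trial status, before outcome results are seen.

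The chi-square test can stay. No other change to the analysis method or to the start of the follow-up clock is needed for this point.

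The cost is a few sentences. The 132 participants and the stated power are kept, whereas a Bonferroni split would cost about 15 percentage points of power or about 26-27 more participants per arm (92-93 against 66). The downside is small: an effect seen only at 6 or 12 months could no longer be claimed as confirmatory.
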